### Study design and setting

This is a 12-week pilot, randomized, double-blind, two-arm, placebo-controlled, parallel-group, multicenter clinical trial that will be conducted in Gachon University Gil Korean Medical Hospital, Korean Medical Hospital of Sangji University, Semyung University Second Affiliated Korean Medical Hospital at Chungju, Kyung Hee University Korean Medical Center, and Kyung Hee University Korean Medicine Hospital at Gangdong in Korea.

A written informed consent will be obtained from each subject by the principal investigator (PI) or researcher after the subject has received sufficient explanation and a period of time in which to make a thoughtful decision. Each subject will be screened up to 7 days prior to randomization. Once they receive the trial subject identifier, they will be treated for 8 weeks and asked to visit the site every 4 weeks for safety and efficacy assessments. A follow-up visit will occur at 4 weeks after the end of the administration. The participants will be asked to return any unused investigational drugs at visit 3 and visit 4 in order to calculate drug compliance. During the trial, the participants will be prohibited from receiving other medications related to CHHF. The protocol design is based on the Consolidated Standards of Reporting Trials (CONSORT) guidelines and Standard Protocol Items: Recommendations for Interventional Trials (SPIRIT) checklist (see Additional file 1). Figure 1 presents a schematic flow diagram of the study.

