### Randomization

Suitable participants, who agree to participate in this RCT, will be randomly assigned to a treatment group (SDT) or a placebo group at a 1:1 ratio. Thirty subjects will each be allocated to the SDT and placebo groups. A web-based randomization system (WBRS) developed by the contract research organization (CRO), the Institute of Safety and Effectiveness Evaluation for Korean Medicine (ISEE), will perform the assignment. The random order will be generated by the CRO’s independent professional statistician using the SAS 6.1 program and stratified by the hospital using random block sizes of two and four based on the allocation code provided by the SAS system.

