#### Secondary outcome measure

The change in the BT and WHOQOL-BREF score between visit 2 (baseline) and visit 4 (after treatment) will be used as the secondary outcome measure. The mean difference between the change scores of the two groups will be calculated.

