#### WHOQOL-BREF

The Korean version of the WHOQOL-BREF is comprised of a 26-item questionnaire estimating quality of life. It assesses five areas: general quality of life, psychological health, physical health, environmental health, and social relationships [16]. The WHOQOL-BREF will be conducted at visits 2, 4, and 5.

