### Statistical analysis

#### Efficacy assessment

For the efficacy assessment of this trial, both intention-to-treat (ITT) and per-protocol (PP) analyses will be performed. Missing data will be adjusted using the last-observation-carried-forward (LOCF) imputation method on ITT analysis. For the safety assessment of this trial, PP analysis will be conducted. The continuous variables will be expressed as the mean ± SD and the nominal variables will be reported as percentages. The ITT method will include all randomly assigned subjects, regardless of any protocol violations or study dropouts. The PP method will include only the subjects who have completed the 12-week study period without any major protocol violations and who have a compliance rate of ≥ 70%. The baseline characteristics will be compared by either a chi-square test for nominal variables or analysis of variance (ANOVA) for continuous variables. For the within-group analysis, the primary and secondary outcome variables will be assessed using a paired *t* test. The between-groups analysis after 8 weeks of administration will be performed using a repeated-measure ANOVA for the primary outcome variables, and a paired *t* test for the mean difference in the VAS score between the SDT group and the placebo group. As a secondary outcome variable, the mean differences in BT and WHOQOL-BREF scores between the groups will be analyzed using a repeated-measure ANOVA for BT and an ANOVA and post-hoc analysis for the WHOQOL-BREF scores. For all non-normal distribution data, a nonparametric statistical test will be performed. SPSS for windows version 23.0 (SPSS Inc., Chicago, IL, USA) will be used for statistical analysis. The statistical significance level will be set at *P* < 0.05.

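### The WHOQOL-BREF test is named as an ANOVA with post-hoc analysis, but with two arms and one change score the post-hoc step has no between-group comparison to make

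*Protocol article*

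**What the plan says.** Under Study design and setting, the trial is described as a "randomized, double-blind, two-arm, placebo-controlled, parallel-group, multicenter clinical trial". Under Randomization: "Thirty subjects will each be allocated to the SDT and placebo groups".

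The Secondary outcome measure section fixes the endpoint: "The change in the BT and WHOQOL-BREF score between visit 2 (baseline) and visit 4 (after treatment) will be used as the secondary outcome measure". It also fixes the contrast: "The mean difference between the change scores of the two groups will be calculated".

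On collection, the WHOQOL-BREF section states "The WHOQOL-BREF will be conducted at visits 2, 4, and 5", and on content: "It assesses five areas: general quality of life, psychological health, physical health, environmental health, and social relationships".

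The Efficacy assessment section then says that "the mean differences in BT and WHOQOL-BREF scores between the groups will be analyzed". The methods which that sentence goes on to name for the two outcomes are these: "using a repeated-measure ANOVA for BT and an ANOVA and post-hoc analysis for the WHOQOL-BREF scores". It does not name the factors of the WHOQOL-BREF ANOVA, whether its response is the change or the visit scores, or what the post-hoc analysis compares.

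**The concern.** A post-hoc analysis after an ANOVA locates differences among three or more means. Two arms compared on one change score give two means and a single contrast, so the named method and the defined outcome do not match.

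The mismatch matters because someone who takes the instruction literally has to find extra cells for the post-hoc step. The visits are an obvious source: WHOQOL-BREF is collected three times, and the same sentence gives body temperature a repeated-measures ANOVA but WHOQOL-BREF a plain one. A plain ANOVA with visits as levels would count each woman two or three times as if she were different people. That can inflate false positives or remove most of the power, depending on which term is read.

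**Working it through.** **Inputs from the protocol article.** Two arms, 30 per arm (Randomization); outcome is the visit 2 to visit 4 change (Secondary outcome measure); WHOQOL-BREF at visits 2, 4 and 5; significance level 0.05 (Efficacy assessment).

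**Assumptions, because the article gives none for WHOQOL-BREF.** Normal scores, SD 1 at each visit, the same within-woman correlation ρ between any two visits, full data on 30 per arm. Where an effect is needed, it is 0.5 SD at visits 4 and 5.

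**The plan's own figure.** There is none for WHOQOL-BREF. The 30 per arm rests on the VAS: 2 × (15.255 × (1.960 + 0.842) / 11.85)² = 26.02, and 26.02 / 0.87 = 29.9, so 30. The 80% power used here is assumed; the article states none. Nothing below alters this figure.

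**Reading A: two-group ANOVA on the change score.**
- With two groups, F = t². In a generated data set with 30 per arm, F = 3.655 = 1.912², and both tests gave p = 0.0608.
- Simulated type I error (10,000 trials per setting) was 0.048 to 0.054 for ρ from 0 to 0.9. It was 0.046 when both arms improved by 0.5 SD and 0.052 with a 0.3 SD baseline imbalance (both at ρ = 0.7).
- Precision at ρ = 0.7:
  - Change score: variance 2(1 − ρ) = 0.60; standard error of the arm difference √(0.60 × 2/30) = 0.200; 0.5 / 0.200 = 2.50.
  - ANCOVA on the visit 2 score: residual variance 1 − ρ² = 0.51; standard error √(0.51 × 2/30) = 0.184; 0.5 / 0.184 = 2.71.
  - Simulated power: 0.69-0.70 for the change score, 0.75 for ANCOVA.
- The variance ratio, ANCOVA to change score, is (1 + ρ)/2: 0.75 at ρ = 0.5, 0.85 at 0.7, 0.90 at 0.8.

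**Reading B: arm and visit (2, 4, 5) as ordinary factors, all scores treated as independent.**

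*Arm term.* The true variance of the three-visit arm difference is (1 + 2ρ) times what the model assumes. The rejection rate with no SDT effect is therefore about 2Φ(−1.96/√(1 + 2ρ)).

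| ρ | 1 + 2ρ | Formula | Simulated |
|---|---|---|---|
| 0.5 | 2.0 | 0.166 | 0.166 |
| 0.7 | 2.4 | 0.206 | 0.206 |
| 0.9 | 2.8 | 0.241 | 0.243 |

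This term also targets the average level over visits, not the change.

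*Arm-by-visit term.* Over visits 2 and 4 alone this is the contrast in the Secondary outcome measure section, but with the wrong error variance. The model assumes a standard error of √(4/30) = 0.365, so the difference must exceed 1.96 × 0.365 = 0.716. The true standard error at ρ = 0.7 is 0.200. Power for a 0.5 SD effect is Φ((0.5 − 0.716)/0.200) = Φ(−1.08) = 0.14. Simulation gave 0.15 over visits 2 and 4, and 0.08 over visits 2, 4 and 5, against 0.69 for the change-score test.

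*Omnibus test over six arm-by-visit cells.* With no SDT effect but both arms improving by 0.5 SD (an assumption), it rejected in 64% of trials at ρ = 0.7.

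**The case against.** The strongest defence is that the article supports Reading A. The sentence applies the test to between-group mean differences, and the Secondary outcome measure section defines these as differences in change scores. The article also uses plain ANOVA for continuous baseline variables with the same two arms, so ANOVA alone does not imply three or more cells. The contrast with body temperature can be turned round: the authors knew the term repeated-measures ANOVA and did not use it here, which may mean that visits are not levels. And post-hoc analysis might mean follow-up across the five WHOQOL-BREF areas.

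Most of this stands. A reader might infer that the plan pools visits as independent observations and so tests a different null hypothesis. The document does not say so, and Reading A is at least as natural. Nor would every term under Reading B test another null: arm-by-visit over visits 2 and 4 tests the right one, with the wrong variance. The article is also condensed, and the factor structure of a secondary analysis is often left to fuller documents.

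What the defence does not remove is the mismatch in the stated text. Under Reading A the post-hoc step cannot be carried out. Under the five-areas reading, comparing areas with one another does not answer the SDT-placebo question, and those scores also come from the same woman. The paragraph gives no assurance that paired and independent structures are kept apart: its preceding sentence assigns a paired t test to the VAS difference between two independent arms.

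**Conclusion.** The point holds as a poorly fixed method for a secondary outcome: a post-hoc step is prescribed where two arms and one change score leave it no between-group comparison, and the wording does not shut out an invalid analysis.

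The size depends on the reading. Under the two-group ANOVA on change, the error rate is nominal and the loss is a redundant step plus some precision (about 70% against 75% power at ρ = 0.7 and a 0.5 SD effect). Only if visits enter as ordinary levels do the larger figures apply: 17-24% false positives on the arm term for ρ of 0.5 to 0.9, and 8-15% power on the arm-by-visit term. The 64% omnibus figure further requires a sizeable common improvement and an analyst who reports the six-cell test as the treatment comparison, so it should not be quoted as the expected error. All these figures rest on assumed correlations and effects.

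The primary outcome and the sample size are not affected.

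**What to change.** In the Efficacy assessment section, replace the WHOQOL-BREF phrase with: *the visit 4 WHOQOL-BREF score will be compared between the SDT and placebo groups by ANCOVA with the visit 2 score as covariate, reported as the between-group difference with 95% CI.* Delete the post-hoc step.

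A two-sample comparison of the visit 2 to visit 4 change is a valid, simpler alternative that matches the outcome definition literally, with somewhat less precision. If visit 5 is also analysed, use a model with a within-woman error term and report the visit 4 group contrast. If the post-hoc step was meant as follow-up by area, say so and define it as an SDT-placebo contrast within each area.

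The cost is a wording change before database lock. The visit 2 score is already collected, and no extra visits, data or participants are needed. What is given up is the option of reporting omnibus or post-hoc significance from pooled visits.

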#### Safety assessment

Safety analysis will be conducted on all subjects who will be randomized and visited at least once after screening. Safety-related measures will be analyzed using the ITT method. The safety data will be stratified according to the symptoms.

### Data management and monitoring

All records will be collected in paper case report form (CRF) files. To protect confidentiality, the files are stored in a secure and locked place and manner. The subject identification and privacy information will be deleted from all study documents. Once the trial is completed, a double independent data entry will be performed for promoting the data quality. After finishing the data entry and dealing with the query, the database will be locked and analyzed by an independent statistician of the ISEE under the confirmation of the PI. Site investigators will have direct access to the final data sets from their own sites.

Monitoring will be performed by the CRO (the ISEE). Monitoring will begin after the first participant completes the entire course of the study. All institutions conducting clinical trials will be monitored in accordance with the SOPs during the course of the clinical trials. Range checks for data values and double data entry will be performed to improve the data quality. No auditing will be performed for this trial.

## Discussion

CHHF has close relationships with Raynaud’s phenomenon (RP) as they both have common symptoms of coldness in the hands and feet. According to one study, 43% of CHHF patients in Korea had RP [18], and many family practitioners prescribe medicines for CHHF according to the treatment recommendations for RP [19]. These reports indicate that CHHF can be considered a potential symptom of RP.

RP refers to transient vasospasm of the peripheral arteries, with pallor changes followed by cyanosis and erythema. It is reported that 3–5% of the population can be affected, and that RP can be hereditary [20]. RP is categorized as primary or secondary RP, depending on the presence or absence of underlying diseases such as connective tissue disease [21]. The pathophysiology of RP is not yet clearly understood. A major factor contributing to the development of RP is considered to be the dysregulation of vasomotor activity, which results in an imbalance between vasoconstriction and vasodilation [22].

Traditional herbal medicine is commonly used in the treatment of CHHF in Korea. According to traditional Korean medicine, CHHF is one symptom constituting the cold syndrome pattern. Therefore, Korean medicine is not only aimed at symptom improvement, but is also prescribed to balance the whole body [23].

SDT is a frequently prescribed herbal formula in Korea. Chen Shiwen first described it in *Prescriptions from the Great Peace Imperial Grace Pharmacy*, the classic Chinese medical book from 1107 [24]. SDT consists of 10 herbs: Poria Sclerotium, Cnidii Rhizoma, Cinnamomi Ramulus, Rehmanniae Radix Preparata, Astragali Radix, Paeoniae Radix, Atractylodis Rhizoma Alba, Ginseng Radix Alba, Angelicae Gigantis Radix, and Glycyrrhizae Radix [25]. It is commonly used for the treatment of CHHF by tonifying the qi and blood [24]. In addition, the classic Chinese medical text *The Yellow Emperor’s Inner Classic* describes the notion of the “spleen and four extremities,” which explains that the spleen functions to regulate the four limbs [26, 27]. Through this notion, limb dysfunction is therefore indicative of splenic problems, and we can postulate that frequent use of SDT for the treatment of CHHF is related to the regulation of spleen function with gastric protective action. Despite the wide use of SDT in the treatment of various diseases including CHHF, no RCT has been performed to assess the clinical efficacy of SDT in the treatment of CHHF. Therefore, evaluation of the efficacy and safety of SDT in the treatment of CHHF is necessary.

For evaluation of the outcome, the VAS score will be used as a primary outcome measure, and the BT as measured by thermometer and the WHOQOL-BREF, a questionnaire estimating quality of life, will be used as secondary outcome measures. There are some limitations of this study. The first is the limited use of outcome measurement methods. Outcome measures such as infrared thermography, the cold stress test (CST), distal–dorsal difference assessment, and heart rate variability analysis have not been applied. Another limitation is the absence of laboratory tests to exclude RP. Due to difficulties in acquiring accurate measurements, RP is likely to be misdiagnosed as a symptom of CHHF. Our team previously performed a pilot study [28] of CHHF and *Danggui-SayukGa-Osuyu-Saenggang-tang*, and conducted the CST and antinuclear antibody test to exclude RP patients. However, very few subjects were excluded by the test, and only the expenditure of the research grant was increased. Therefore, in the current trial, we will not include these tests. In the near future, our team will prepare for further large-scale clinical trials searching for methods to accurately distinguish CHHF from primary RP. Despite these limitations, as the first study to assess the efficacy and safety of SDT in the treatment of CHHF, we expect that this study will provide basic clinical information regarding Korean herbal medicine treatment of CHHF and that this study protocol will be the basis for designing a full RCT.

## Trial status

Participant recruitment began on 31 January 2018, and 50 participants have been recruited until now. Recruitment will complete in May 2020. The protocol version 1.2 (1 December 2018) is currently active.

## Abbreviations

AE: Adverse event
ALT: Alanine aminotransferase
ANOVA: Analysis of variance
AST: Aspartate aminotransferase
BT: Body temperature
CHHF: Cold hypersensitivity in the hands and feet
CRO: Contract research organization
CST: Cold stress test
DBP: Diastolic blood pressure
hCG: Human chorionic gonadotropin
ISEE: Institute of Safety and Effectiveness Evaluation
ITT: Intention to treat
PP: Per protocol
RBC: Red blood cell
RCT: Randomized clinical trial
RP: Raynaud’s phenomenon
SAE: Serious adverse event
SBP: Systolic blood pressure
SD: Standard deviation
SDT: *Sipjeondaebo-tang*
SOP: Standard operating procedure
TSH: Thyroid-stimulating hormone
VAS: Visual Analogue Scale
WBC: White blood cell
WBRS: Web-based randomization system
WHOQOL-BREF: World Health Organization Quality of Life Scale Abbreviated Version
